#### Primary outcome measures

This will include percent success in reaching BP control (Table 2) and changes in clinic BP measurements.

**Table 2 Tab2:** Definition of outcome measures

Variable	Definition
Blood pressure control	Clinic blood pressure control will be defined at resting systolic blood pressure of <140 mmHg and or diastolic blood pressure of <90 mmHg
Medication adherence	Medication adherence will be categorized using Medication Possession Ratios into: Excellent 100 % Good 80–99 % and Poor <80 %.

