#### Proposed sample size

For this feasibility cluster RCT we will recruit 15 patients per cluster (i.e., physician), 30 patients per group (intervention versus control group) (total *n* = 60). We agree with Kraemer et al. [57] that pilot feasibility studies are deficient in estimating effect size with sufficient accuracy for future study design. To this end we will evaluate the availability of subjects, assess proportions approached/consented, and examine the feasibility of PINGS by evaluating adherence and retention rates. Thus, sample size justification focuses on the precision of estimates rather than the power of statistical tests. We will recruit 30 subjects (15 per physician = cluster) per treatment group based on number of degrees of freedom within each cluster, as suggested by Mead, to obtain reasonable precision for variance estimates [58].

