#### Recruitment

A list of eligible patients will be identified from hospital medical records by a research assistant (RA) with the identity of the patients’ doctors not included. The research coordinator (RC) will contact and schedule eligible patients for screening/recruitment and obtain informed consent voluntarily from patients who are interested in the study. Subjects whose SBP averages ≥140 mmHg from the last two readings of the 10-min protocol will have their height, weight and waist circumference measured. A set of questionnaires will be administered to assess study outcome measures (see Table 1). The study site admits an average of 43 stroke patients each month. Based upon the stroke with HTN incidence patterns in the KATH and SMASH pilot work [38–40, 47], we will recruit eight patients (four intervention group patients and four control group patients) per month for enrollment into the study.

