#### Primary outcome measures

For these measures, generalized linear mixed models (GLMM) will be used to compare the two groups with group as primary independent variable and percent success reaching BP control (or resting BP changes individually) as the primary dependent variable (Table 2) [64]. GLMM allow for missing data, measurement at different times and take into account the effect of clustering, i.e., correlation of repeated measurements within patients clustered within MD (Medical Doctor) provider. Group and time (baseline, 3, 6 and 9 months) will be fixed effects; demographics and secondary outcome measures (e.g., medication adherence via the MPR) will be adjustment covariates. We will assess changes over time via a time-by-intervention interaction term in multivariable models. We will estimate differences (for means or proportions) in ancillary moderator and mediator measures between the two groups via 95 % CIs as appropriate (e.g., self-efficacy, autonomous regulation, and so forth.). We will estimate differences (via 95 % CI) in proportions and average slopes between intervention versus control groups and evaluate linearity of trajectories as input for future RCT analysis strategy. We will estimate percent success reaching BP control for each subject over the trial (baseline, 3, 6 and 9 months), and the within-subject longitudinal trajectories (e.g., slopes), and then summarize as mean longitudinal trajectory within each treatment group (e.g., mean slopes with 95 % CI). Intracluster correlation coefficient (ICC) and variance estimates will be obtained of efficacy outcomes and covariance structure of the longitudinal scores for determination of sample size (and hence adequate power) for a future RCT. Multiple imputation methods will be used for missing end-of-study outcomes. Dropout rate, both selective and differential, is an important issue. If more than 10 % of data are missing, we will add an intermediate evaluation point in a future RCT to provide more data for use in endpoint imputation.

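### For binary BP control, baseline is kept as an outcome visit although the entry criterion fixes it at zero, so contrasts against baseline cannot be estimated and slopes absorb a built-in rise

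*Protocol article*

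**What the plan says.** The Inclusion criteria section of the protocol article requires uncontrolled hypertension, defined as SBP of 140 mmHg or more. The threshold applies at the last pre-stroke encounter, after the stroke, and at the screening/recruitment visit. The Recruitment section says how that reading is taken. Measurement of height, weight and waist goes on for "Subjects whose SBP averages ≥140 mmHg from the last two readings of the 10-min protocol".

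Table 2 defines control as "resting systolic blood pressure of <140 mmHg and or diastolic blood pressure of <90 mmHg".

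Under Statistical analyses, Primary outcome measures, the generalized linear mixed model takes "percent success reaching BP control (or resting BP changes individually) as the primary dependent variable". On the time factor it says "Group and time (baseline, 3, 6 and 9 months) will be fixed effects". On change it says "We will assess changes over time via a time-by-intervention interaction term in multivariable models". Baseline appears again in the per-subject summary: "We will estimate percent success reaching BP control for each subject over the trial (baseline, 3, 6 and 9 months". The same section also plans slopes: "We will estimate differences (via 95 % CI) in proportions and average slopes between intervention versus control groups and evaluate linearity of trajectories".

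Nothing in the article removes baseline from the binary outcome or makes it a covariate there.

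**The concern.** An outcome that selection fixes at one value carries no information at that visit. For BP control, the entry rule and the outcome definition use the same SBP cut-point, so baseline control is zero in both arms before any treatment is given. A logistic model that estimates a separate level for that visit has to estimate the log-odds of zero. Contrasts that use baseline as the reference inherit the problem, including the baseline-referenced group-by-time terms that would naturally be read as the effect on change.

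The per-subject percentages and slopes have a related fault: part of the rise in each arm comes from the entry criterion. The article intends these estimates as input to the future trial, so a distorted trajectory or an unusable interaction would be carried forward.

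**Working it through.** **Inputs from the article.** The Proposed sample size section gives "15 patients per cluster (i.e., physician), 30 patients per group (intervention versus control group". Four physicians × 15 = 60, or 30 per arm, which agrees with the stated total. The article gives no power or effect-size figure to reproduce. The time levels are baseline, 3, 6 and 9 months.

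**Assumed inputs.** The article gives no expected control rates for this trial, so follow-up counts were assumed: 12, 13 and 12 of 30 in the control arm (40%, 43%, 40%) and 18, 20 and 19 of 30 in the intervention arm (60%, 67%, 63%). Baseline is 0/30 in each arm. A second run used 20% v 93% at every follow-up visit.

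**Step 1: categorical time with interaction, by hand.** The saturated logistic model reproduces each cell's log-odds.
- Baseline: log(0/30) is minus infinity in each arm.
- Group effect at month 3: log[(18/12)/(12/18)] = log 2.25 = 0.81, with SE √(1/18 + 1/12 + 1/12 + 1/18) = 0.53.
- Month 6: log[(20/10)/(13/17)] = 0.96, SE 0.53. Month 9: log[(19/11)/(12/18)] = 0.95, SE 0.53.
- Group × month 3 against baseline: 0.81 minus the difference of two infinite log-odds, which is undefined.
- Month 6 minus month 3 in the group effect: 0.96 − 0.81 = 0.15, SE 0.75, which is finite.

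**Step 2: what the software does** (ordinary logistic fit, no random effects).

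| Iterations | Baseline intercept | SE of group × month 3 |
|---|---|---|
| 5 | −6.6 | 4.2 |
| 10 | −11.6 | 51 |
| 20 | −21.6 | 7,548 |
| 25 | −26.6 | 91,951 |

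These values depend on where the fit is stopped and have no meaning of their own. The 20% v 93% run diverges in the same way.

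**Step 3: does a random effect help?** In a random-intercept logistic model (patient level only, no physician effect), the log-likelihood only flattens as the common baseline logit falls: −122.10 at −3, −118.03 at −8 and −117.99 at −20. Three pairs of baseline logits (control, intervention) fit almost equally well:

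| Baseline logits | Log-likelihood | Group × month 3 |
|---|---|---|
| −12, −20 | −117.9918 | 9.0 |
| −20, −12 | −117.9918 | −7.0 |
| −20, −20 | −117.9915 | 1.0 |

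The data do not determine this term.

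**Step 4: no interaction.** With group and categorical time only, the group log-odds ratio is 0.908 (SE 0.307) whether the baseline rows are kept or dropped. Only the intercept and the time terms diverge.

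**Step 5: linear time, baseline included.** All terms are finite (group × month 0.091 per month, SE 0.093). Fitted baseline control is 14% and 19% against 0% observed; in the 20% v 93% run it is 7% and 16%.

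**Step 6: per-subject percent success.** If it is averaged over all four visits, a patient controlled at every follow-up visit scores 3/4 = 75%, which is the maximum.

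**Step 7: months 3, 6 and 9 only.** Every term is finite: group at month 3 = 0.81 (SE 0.53), group × month 6 = 0.15 (SE 0.75), group × month 9 = 0.14 (SE 0.75).

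**The case against.** The strongest reply is that the group comparison survives. The article names group as the primary independent variable and introduces the interaction in a separate sentence, for change over time. Steps 1 and 4 bear this out. A reader might infer that the whole primary model fails, or that all time and group-by-time terms are lost. The documents do not support that: only contrasts involving baseline are lost.

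Second, the problem rests on readings that the article does not fix.
- Under an 'or' reading of Table 2, a patient with SBP of 140 or more and DBP below 90 counts as controlled at baseline. With an assumed 3 to 9 of 30 such patients per arm, all terms are finite (SE of group × time about 0.8 to 1.0 at the milder rates). That reading, however, would enrol a patient as uncontrolled and score the same reading as controlled, which conflicts with the article's own SBP-based entry definition.
- The article does not say that the screening reading is the baseline value, though it describes no separate one.
- It states neither a logit link nor categorical time, and it speaks of slopes and linearity. Linear time avoids divergence but fits the forced zero badly.

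Third, the same sentence governs resting BP, where there is no separation and where keeping baseline in the response is an accepted approach. This stands.

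Fourth, the 75% ceiling applies only if percent success is averaged within patient over all four visits; the sentence can also be read as an estimate at each visit. A zero common to both arms also does not by itself favour either arm in the slope difference. Both points stand.

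Link, time coding and reference level may be settled in an analysis plan that is not shown. That answers some of the detail, but not the stated inclusion of baseline as an outcome visit for BP control, which the article makes twice.

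**Conclusion.** The point holds for the binary BP-control outcome only. If control requires SBP below 140 and the qualifying reading is the baseline value, baseline control is 0/60 by design. With a logit link, categorical time and group-by-time, the time terms against baseline then have no finite estimate or usable Wald test. Nor do the group and group-by-time coefficients when baseline is the reference. The group effects at months 3, 6 and 9, the differences among those visits, and the group effect without interaction are unaffected. With linear time the estimates exist, but they misfit baseline and include in both arms a rise that the entry criterion creates.

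The numerical sizes rest on assumed control rates. The lack of a finite baseline contrast does not: it follows from the zero cells alone.

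This is a should-fix. The trial is a feasibility pilot justified by precision rather than power, but its slopes, interaction and variance estimates are meant to inform the next trial.

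**What to change.** - Model binary BP control at months 3, 6 and 9 only, with group, categorical visit, group-by-visit and continuous baseline SBP as a covariate. Keep the planned handling of repeated measures and physician clustering.
- Compute percent success and BP-control trajectories from post-baseline visits only.
- Reconcile the 'and or' in Table 2 with the SBP-based definition of uncontrolled hypertension used for entry, and state which reading is the baseline value.
- Leave the continuous BP model as it is on this ground.

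The cost is a change of wording in the analysis section and Table 2. SBP is already measured at recruitment, so no new data, visits or patients are needed. The binary model gives up only contrasts with a visit at which the outcome could not vary.

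### The continuous primary comparison reduces to a change-score contrast, because measured baseline BP is neither a covariate nor held to a common mean across arms; adjusting for it would give modestly narrower intervals at almost no cost

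*Protocol article*

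**What the plan says.** Under Outcome measures, the primary outcomes are "percent success in reaching BP control (Table 2) and changes in clinic BP measurements". The analysis section fits generalized linear mixed models with "percent success reaching BP control (or resting BP changes individually) as the primary dependent variable".

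The rest of the model is set out in the same paragraph:

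- Fixed effects: "Group and time (baseline, 3, 6 and 9 months) will be fixed effects".
- Covariates: "demographics and secondary outcome measures (e.g., medication adherence via the MPR) will be adjustment covariates".
- Interaction: "We will assess changes over time via a time-by-intervention interaction term in multivariable models".
- Correlation: the model is to allow for "correlation of repeated measurements within patients clustered within MD (Medical Doctor) provider".

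Baseline SBP is available for every patient, because entry depends on it. Recruitment refers to "Subjects whose SBP averages ≥140 mmHg from the last two readings of the 10-min protocol", and the analysis section itself lists baseline among the visits. Baseline BP is not named as a covariate, and nothing says that the two arms share a baseline mean.

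**The concern.** Two features of the text do not fit together. If the response is change from baseline, a baseline row has the value zero for every patient and carries no information. If the response is BP itself, baseline is a genuine visit, but the text does not call BP the response. The article should say which is meant.

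On either reading the arms are compared on their mean change, with no conditioning on where each patient started. Follow-up BP usually depends on baseline BP with a slope below 1. Subtracting the whole baseline value then removes too much. This adds noise and carries part of any chance baseline difference into the estimate with the opposite sign.

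Precision is at stake. The sample size is justified by the precision of estimates, not by power, so interval width is what the trial is meant to deliver.

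**Working it through.** **The plan's own figure.** 2 arms × 2 physicians × 15 patients = 60, as stated under Proposed sample size. The article gives no effect size, BP SD, baseline-to-follow-up correlation or ICC, so everything below rests on stated assumptions.

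**Step 1: what the written model estimates.**

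- *Response is BP change.* The baseline row is zero in both arms. The interaction at a later visit, measured against baseline, is (mean change, intervention) − (mean change, control).
- *Response is BP level, with group, time and their interaction unconstrained.* With complete data, each fitted arm-by-visit mean is the observed mean, so the interaction is again the difference in mean changes.

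A simulated complete data set (60 patients, four visits, correlation 0.4, SD 1) confirms the second case:

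| Analysis at the last visit | Estimate | SE |
|---|---|---|
| Unconstrained group-by-time contrast | 0.2041 | 0.283 |
| Simple difference in mean change | 0.2041 | – |
| Common baseline mean for both arms | 0.1776 | 0.237 |

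The first two estimates are identical. The third equals the follow-up difference minus 0.4 times the baseline difference, which is the baseline-adjusted estimate.

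**Step 2: cost in precision, allowing for the entry rule.** Assume SBP in the source population has mean 155 and SD 20 mmHg at baseline and follow-up, with correlation ρ, so the slope of follow-up on baseline is ρ. Patients enter only if baseline is at least 140. (This is a simplification: the inclusion criteria also require a raised SBP at earlier encounters.)

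- Standardised cut: (140 − 155)/20 = −0.75.
- λ = φ(0.75)/Φ(0.75) = 0.3011/0.7734 = 0.389.
- Baseline variance kept after truncation: k = 1 − 0.75 × 0.389 − 0.389² = 0.556, so the baseline SD is 20 × √0.556 = 14.9 mmHg.
- Change-score variance, in units of SD²: (1 − ρ²) + (1 − ρ)²k.
- Baseline-adjusted variance: 1 − ρ².
- Ratio, adjusted to change score: (1 + ρ)/[(1 + ρ) + (1 − ρ)k].

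| ρ | Ratio | √Ratio | Interval narrower by |
|---|---|---|---|
| 0.3 | 1.3/(1.3 + 0.389) = 0.77 | 0.88 | 12% |
| 0.5 | 1.5/(1.5 + 0.278) = 0.84 | 0.92 | 8% |
| 0.7 | 1.7/(1.7 + 0.167) = 0.91 | 0.95 | 5% |

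**Step 3: in mmHg, at ρ = 0.5 with 30 per arm and before any clustering.**

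- Change score: 2.00 × 20 × √0.889 × √(2/30) = 9.7.
- Baseline-adjusted: 2.00 × 20 × √0.75 × √(2/30) = 9.0, rounded up from 8.95.

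**Step 4: chance imbalance.** The error left in the change score is −(1 − slope) × baseline difference. A 5 mmHg difference at slope 0.5 leaves 2.5 mmHg. The SE of the baseline difference is √[(2/30)(1 + 14 × ICC)]: 0.26 SD at ICC 0, 0.34 SD at 0.05 and 0.40 SD at 0.10. With the truncated SD of 14.9, these are about 3.9, 5.0 and 6.0 mmHg, so 5 mmHg would not be unusual.

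**Step 5: BP control.** Everyone enters with SBP of at least 140. Table 2 joins its systolic and diastolic thresholds with both conjunctions. If both must be met, every patient is uncontrolled at baseline, and a logistic interaction against baseline cannot be estimated. If either suffices, some patients count as controlled at entry through diastolic pressure alone. In both cases a patient entering at 142 and one at 190 can have the same baseline status.

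**The case against.** The best defence is that baseline is not ignored. It is a level of time in a repeated-measures model with within-patient correlation, and the interaction compares changes from it. If BP level is the response, that is a standard analysis, and choosing a covariate or a common baseline mean instead is a matter of efficiency. This stands, and it limits the point to precision and clarity. A fuller covariate list might be left to an analysis plan, but this article does state the response, visits, interaction and covariates, and what it states leads to the change-score contrast.

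A reader might infer more than the document supports:

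- **That the group difference is biased or inflated.** It is not, under randomisation. Only its variance rises.
- **That selection at SBP ≥140 biases the comparison through regression to the mean.** The rule applies to both arms, so in expectation the effect cancels.
- **That chance imbalance goes uncorrected.** Differencing subtracts all of it. The fault is over-correction.
- **That the effect is diluted to three quarters.** This needs zero-valued baseline rows and also a group effect averaged over four visits. The article assesses change through the interaction, which is not diluted in this way.
- **That the next trial will be sized on too large a variance.** The article plans to estimate the longitudinal covariance structure, from which an adjusted variance can be derived.
- **That the gain is larger.** Without truncation the variance ratios are 0.65, 0.75 and 0.85 (intervals 19%, 13% and 8% narrower), but that describes patients whom the entry rule excludes.
- **That the BP-control analysis gains similarly.** The variance formula does not carry over to a logistic model, where a covariate also changes the conditional odds ratio. No gain is shown there.

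**Conclusion.** The point holds as one of efficiency and clarity. The text pairs BP change with a baseline visit at which change is zero, and it leaves out baseline conditioning in either of its usual forms. The resulting contrast is valid under randomisation but less precise than it could be. With an assumed mean of 155 and SD of 20 mmHg truncated at 140, the avoidable width is about 5% to 12% for correlations from 0.7 down to 0.3, or roughly 0.8 mmHg of half-width at 0.5. The true size depends on an SD, correlation and ICC that the article does not give.

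Two limits apply. If physicians are the randomised unit, the arm comparison has 4 − 2 = 2 between-cluster degrees of freedom, and adjustment does not change that. Trial design randomises physicians, whereas Allocation and concealment randomises patients in blocks of four, so the documents do not settle which applies. Adjustment for post-randomisation measures such as the MPR, stated in the same sentence, is a separate problem.

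**What to change.** In Statistical analyses, Primary outcome measures, replace BP change as the response with one of two explicit models:

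1. Clinic SBP, and separately DBP, at months 3, 6 and 9, with the patient's own baseline value of that measure as a covariate, plus group, time, group-by-time, and patient and physician random effects.
2. SBP and DBP at all four visits, with the two arms constrained to a common mean at baseline.

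For BP control, model months 3, 6 and 9 only and include baseline SBP as a prognostic covariate. The reason is that the entry rule leaves little or no variation in control at baseline, not a demonstrated gain in precision.

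The cost is a few sentences and one degree of freedom. No new data are needed and the sample size stays at 60. Stating in the same revision which unit is randomised would let readers see how far the precision gain carries through to the arm comparison.

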## Background

Hypertension (HTN) is the premier modifiable risk factor for recurrent stroke [1]. Fortunately, with control of HTN [2], recurrence of and mortality from stroke can be greatly reduced [3–5] as has been seen in several high-income countries (HICs) [6–9]. However, for low- and middle- income countries (LMICs) that disproportionately bear the global burden of stroke, these gains have not materialized [10]. Data from the Global Burden of Disease 2013 study suggest that deaths and disability-adjusted life years from stroke in LMICs account for 75.2 % and 81.0 % of global estimates, respectively [11].

Achieving and sustaining blood pressure (BP) control is a global challenge [12] particularly in LMICs including sub-Saharan Africa (SSA) [12–14]. A multinational survey has identified that 46.5 % of participants with HTN were aware of the diagnosis and 32.5 % of hypertensive participants had their BP controlled, with rates of awareness and control of BP significantly higher in HICs compared with LMICs [12]. Key factors responsible for uncontrolled HTN are medication non-adherence and failure to intensify therapy in a timely manner (i.e., therapeutic inertia) [15, 16]. Furthermore, the lack of availability, poor affordability and low rates of utilization of secondary prevention cardiovascular medicines in LMICs [17, 18] combined with low literacy levels, traditional beliefs and misconceptions about HTN may all contribute to the low prevalence of HTN awareness, treatment and control which poses a serious threat to stroke prevention.

Systematic reviews of randomized controlled trials (RCTs) involving uncontrolled hypertensive patients have indicated that BP self-monitoring, medication-reminding tactics and the use of case managers each improve adherence, therapeutic inertia and BP levels [19–22]. No RCTs looking at medication adherence or BP self-monitoring have been designed specifically for people in SSA, especially for those at high risk for future stroke. However, mobile health (m-Health) technology offers a promising approach to address this need [23–30]. Most adults in SSA own a cell phone (approximately 73 %) [31, 32], smartphone ownership is burgeoning (approximately 35 %) [33], and m-Health has produced promising results in chronic disease management (e.g., HIV) in SSA [34–36].

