### Follow-up phase

Subjects in both arms of the study will be followed up for 6 months after the initial 3-month trial. During the follow-up period, subjects will attend clinics monthly where their physicians will assess them clinically. At months 3, 6 and 9 post enrollment patients and providers will undergo assessments on methodological parameters and consumer responses, clinic BP measurements, medication adherence, health literacy on stroke and HTN as well as self-determination theory constructs such as Autonomous Self-regulation and Competence Scales. Physicians in both groups will also undergo assessment on adherence to BP management protocols (Fig. 1 and Table 1).

**Table 1 Tab1:** Study outcome measures

Outcomes	Psychometrics (internal consistency [α], test-retest reliability [r]) NOTE A^a^	Time points
Primary outcomes		
Feasibility: methodological parameters and consumer responses	Recruitment and retention rates; Self-report: Patient/Provider Satisfaction Scale (.82–.96, test-retest (1 week) .98) [74, 75], fidelity checklists: patient level (e.g., connection; BP uploads via phone; opening of messages/educational information and provider level (e.g., delivery of provider summaries; phone alerts)	Baseline, 3, 6, 9 months
Clinic: BP	Clinic-based BP	
Feedback and refinement	Focus groups	Providers and IG: 9 months
Secondary outcomes		
Medication adherence Physician adherence	Medication Possession Ratio (MPR); Morisky Medication Adherence Scale (α = .76–.83, r = .64) [76, 77], provider guideline adherence: timely med changes (date of script changes following BP feedback (bi-monthly PINGS reports/clinic BPs)	Baseline, 3, 6, 9 months
Self-determination theory constructs	Autonomous Self-Regulation (α = .81–.84, r = .38) [78], Competence Scale (α = .88–.95, r = .32–.46) [51, 52, 78].	
Potential moderators/mediators		
Demographics	Age, education level, income	Baseline
HTN/stroke knowledge, health literacy, anthropometrics	Self-report: HTN/stroke knowledge (.70) [54, 55], health literacy (r = .74, .82) [78–80], Height/ weight/girth	Baseline, 3, 6, 9 months
Medication adherence factors	Side effects, adverse events	As reported, and 3, 6, 9 months

^a^Basic psychometric property analyses (e.g., internal consistency, test-retest reliability) will be conducted during first 3 months on scales, which have not been used with Ghanaian stroke patients

*BP* blood pressure, *HTN* hypertension, *IG* Intervention Group

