#### Secondary outcome measures

These will include outcomes such as MPR, Morisky Medication Adherence Scale (MMAS) score and Competence and Autonomous Self-regulation Scale scores.

Table 1 shows all outcome variables, questionnaires to be used and when they will be administered. We will assess self determination theory-related constructs of competence [48, 49], and autonomous self-regulation [50, 51]. We will also assess HTN knowledge [52, 53], medication side effects, stroke knowledge, self-reported medication adherence (MMAS), beliefs and life goals [54, 55] and MPR [56].

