#### Secondary outcome measures

These are categorical (percent of patients and providers who were adherent) and continuous (e.g., MPR, MMAS score; Competence and Autonomous Self-regulation Scale scores). GLMM will compare the two groups with treatment group as primary independent variable, and outcome measures individually as the dependent variables [64]. Group and time (baseline, 3-, 6- and 9-month visit) will be included as fixed and physician as random effects; health literacy, demographics (age, gender, and so forth) and HTN/stroke knowledge will be adjustment variables. Ninety-five percent CIs will be reported.

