Possible limitations to the PINGS study may include the lack of a longer feasibility trial and a lack of intensive lifestyle programs. In response to the first limitation, our selection of a 3-month trial and 6-month follow-up was guided by BP control trials which usually ran for 1–6 months and had no follow-up [20, 21]. A future efficacy RCT will assess if BP control is sustained beyond 9 months. Our approach to the lack of intensive lifestyle programs will be to first focus on how medication adherence and BP monitoring impact BP control without including additional tactics. This is based upon financial costs, response burden and primary practice-based HTN RCTs which found that: (1) adding lifestyle programs to BP monitoring or medication reminder tactics, and so forth, does not necessarily enhance BP control [70] and (2) lifestyle programs are difficult to implement and sustain [71–73]. Also, providers repeatedly request easy-to-implement and efficacious programs. We will have a wealth of data to address important issues not detailed which will guide our future work (e.g., triangulation of the MMAS self-report, pharmacy records (MPR) data to develop effective algorithms for medication adherence measurement). Additional moderator/mediator (understanding they are perhaps underpowered) analyses will be conducted examining the influence of acculturation, health literacy, HTN/stroke knowledge and so forth upon medication adherence and BP control.

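### The primary BP model adjusts for secondary outcomes such as MPR without limiting them to baseline, so as written its group comparison does not estimate the total effect of PINGS

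*Protocol article*

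**What the plan says.** Under Statistical analyses, Primary outcome measures, the generalized linear mixed model (GLMM) has "group as primary independent variable and percent success reaching BP control" (or BP change) as dependent variable. Group and time are fixed effects, and baseline is one of the four levels of time. The section then states that "demographics and secondary outcome measures (e.g., medication adherence via the MPR) will be adjustment covariates". Nothing there says that baseline values are meant.

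Under Outcome measures, the secondary outcomes are described thus: "These will include outcomes such as MPR, Morisky Medication Adherence Scale (MMAS) score and Competence and Autonomous Self-regulation Scale scores". Table 1 adds physician adherence to the secondary outcomes. It schedules medication and physician adherence at baseline and at months 3, 6 and 9. The Follow-up phase section confirms the later visits: "At months 3, 6 and 9 post enrollment patients and providers will undergo assessments on methodological parameters and consumer responses, clinic BP measurements, medication adherence", followed by the self-determination scales.

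For the secondary-outcome models, "health literacy, demographics (age, gender, and so forth) and HTN/stroke knowledge will be adjustment variables". Table 1 lists health literacy and knowledge as potential moderators or mediators and measures them at the same four times.

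**The concern.** MPR is something the intervention is meant to move. The Background says: "Key factors responsible for uncontrolled HTN are medication non-adherence and failure to intensify therapy in a timely manner". The intervention sections tailor text messages to the previous day's reported adherence and have the nurse contact patients whose adherence falls below .80. The control messages leave medication adherence out, so the arms differ on it by design. The Discussion gives the purpose as to "first focus on how medication adherence and BP monitoring impact BP control without including additional tactics".

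Adjusting a group comparison for a variable that lies between the intervention and the outcome has two consequences. It takes out the part of the effect that passes through that variable. It also links group to any unmeasured cause that adherence and BP share, so what remains is not a clean direct effect either.

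MPR is only the example given. The covariate class is secondary outcome measures, which also takes in the Morisky score, Competence, Autonomous Self-Regulation and physician adherence. Read literally, the sentence can adjust away the provider route (timely medication changes) as well as the patient route.

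At stake is what the BP result means. BP control is a primary outcome, and the Discussion says that a feasible and preliminarily effective intervention would lead to a larger trial. Low power is acceptable in a pilot, but its main model should still estimate the intended quantity.

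**Working it through.** **The plan's own figure.** Four physician clusters × 15 patients = 60, and 2 × 15 = 30 per arm. This reproduces. The sample size rests on precision, and the protocol gives no effect size, SD or power, so nothing in it fixes how large the distortion would be.

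**Inputs.** The model terms and visit times come from the protocol. The mediated share m, the reliability r of MPR within arm, and the values for total effect, SD and MPR used below are assumptions.

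**Formula.** Take continuous BP and a linear model:

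- Total effect of group on BP: D.
- Effect of group on MPR: a. Effect of MPR on BP: b. Then a·b = m·D, and the direct effect is (1 − m)·D.
- If MPR is measured with reliability r, its coefficient in the adjusted model is b·r.
- Adjusted group coefficient = (1 − m)·D + a·b·(1 − r) = D·(1 − m·r).

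Without unmeasured confounding, the share of the total effect left is therefore 1 − m·r:

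| m | r = 1 | r = 0.7 | r = 0.5 |
|---|---|---|---|
| 0 | 100% | 100% | 100% |
| 0.25 | 75% | 82.5% | 87.5% |
| 0.50 | 50% | 65% | 75% |
| 0.75 | 25% | 47.5% | 62.5% |
| 1.0 | 0% | 30% | 50% |

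A simulation with 400,000 patients per setting (D = −10 mmHg, SD 18 mmHg, MPR gain 0.15, within-arm MPR SD 0.15) agreed to within about one percentage point.

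More than half of the effect is lost only if m > 0.5/r. That means m above 0.50 at r = 1 and above 0.71 at r = 0.7. At r = 0.5 it never happens.

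**Shared cause of adherence and BP.** Let an unmeasured factor have loading 0.4 on MPR and on BP, with r = 1. The adjusted coefficient shifts by 18 × 0.4² × (0.15/0.15) = 2.88 mmHg. If the factor raises adherence and lowers BP, the shift is upward:

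- m = 0: −10 + 2.88 = −7.12, so 71% is left although nothing is mediated.
- m = 1: 0 + 2.88 = +2.88, about −29% of the total, a reversed sign. The simulation gave +2.94.

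If the factor raises both adherence and BP, the shift is −2.88 instead. The direction of this bias cannot be fixed from the protocol.

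**After the fix.** Without post-baseline MPR, the coefficient returns D for every m, and n stays at 60.

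**Limits.** The algebra is for continuous BP and a single follow-up time. It does not carry over exactly to a logistic model for BP control or to the repeated-measures model. The conditioning problem does carry over, and it includes the time-by-group term, which holds the post-baseline effect when baseline is a level of time.

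**The case against.** The strongest reply is that the sentence does not declare post-baseline adjustment. Table 1 also collects adherence at baseline, and baseline MPR would be an acceptable covariate. This stands as far as it goes: the fault lies in unrestricted wording. Still, a covariate described as a secondary outcome measure is most naturally read as the follow-up measurement, and the text does nothing to exclude that.

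The same section also plans differences in proportions and average slopes with 95% confidence intervals, not stated to be covariate-adjusted. A total-effect contrast may therefore be reported anyway. That softens the consequence but does not repair the named primary model.

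Three stronger readings are tempting and are not supported:

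- A reader might infer that most of the effect is lost. The protocol gives no mediated share, and it describes routes that need not run through MPR: provider reports, faster regimen changes, and BP self-monitoring with feedback.
- A reader might infer that the better PINGS works on adherence, the nearer the adjusted effect comes to zero. Under linear mediation with MPR measured without error, the adjusted coefficient is the direct effect and does not depend on how far adherence moves. With an assumed direct effect of −6 mmHg and −30 mmHg per unit of MPR, an MPR gain from 0 to 0.4 takes the total from −6 to −6 − 30 × 0.4 = −18, while the adjusted value stays at −6.
- A reader might infer that the decision on a larger trial hangs on this coefficient. The protocol sets no such rule, and its sample size section says that pilots estimate effect sizes poorly. Rejection rates are therefore a poor yardstick here.

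**Conclusion.** The concern holds in this form: the primary model as written conditions the group comparison on secondary outcomes that are measured after allocation and targeted by the intervention, so it does not estimate the total effect of PINGS on BP. The part removed is unknown and possibly large. Without unmeasured confounding it runs from nothing to all of the effect, according to the assumed mediated share and MPR reliability. With a shared cause of adherence and BP, bias is possible even with no mediation, and the sign can reverse.

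For the secondary models the point is conditional. Health literacy and knowledge cause the same difficulty only if their follow-up values are used, and the text does not say which values enter.

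**What to change.** - In the primary model, delete secondary outcome measures (including MPR) from the covariates, or restrict them to baseline values. Adjust only for baseline variables such as demographics.
- Keep baseline BP either as a level of time in the outcome vector, as now, or as a covariate with only post-baseline outcomes. Do not do both in one model.
- In the secondary-outcome models, state that only baseline health literacy and HTN/stroke knowledge are used.
- Report any model that conditions on post-baseline MPR or other secondary outcomes as exploratory mediation work. It would be an addition: the structural equation modeling under Planned refinement of the PINGS program relates competence and autonomous regulation to outcomes that include medication adherence, and does not plan MPR as a mediator.

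The cost is a change of analysis wording. Sample size, visits and data collection stay as they are.
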